## Materials and methods

Study design

This is a single-center, double-blind, placebo-controlled, parallel arms, superiority randomized clinical trial. The maximum duration of the intervention will be 28 days while the duration of follow-up will be till hospital discharge. The study will be conducted in the ICU of the largest government hospital in the central region of Saudi Arabia. The ICU has 110 beds, fully equipped with invasive and non-invasive monitoring and ventilation capabilities. It is covered round the clock by intensivists, with a nurse-patient ratio of 1: 1.

Inclusion and Exclusion Criteria

Inclusion criteria: Adults (≥18 years), ICU admission, mechanical ventilation for <7 days, and ARDS diagnosed within 24 hours per the Berlin Definition [1], which includes: a) Chest x-ray showing bilateral opacities, not fully explained by effusions, lobar/lung collapse, or nodules; b) Respiratory failure not fully explained by cardiac failure or fluid overload, and exclusion of hydrostatic edema (by echocardiography); c) Oxygenation and ventilator settings matching one of the three categories of ARDS: Mild: 200 mmHg < PaO2/FIO2 ≤ 300 mmHg with positive end-expiratory pressure (PEEP) or continuous positive airway pressure (CPAP) ≥ 5 cm H2O. Moderate: 100 mm Hg < PaO2/FIO2 ≤ 200 mm Hg with PEEP ≥ 5 cm H2O. Severe: PaO2/FIO2 ≤ 100 mm Hg with PEEP ≥ 5 cm H2O.

Exclusion criteria: Pregnant or lactating ladies; Patients who are not expected to survive more than 48 hours, according to the treating team; Mechanical ventilation is expected to continue for less than 48 hours (due to rapid recovery) according to the treating team; Advanced directive of Do Not Resuscitate (DNR); Refusal to participate in the trial by the patient or official surrogate; Known allergy to furosemide; Previous enrollment in the trial (a patient can only be enrolled once).

Study objectives

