The primary objective is 28-day mortality in the ICU, starting from the day of randomization. Secondary objectives include: All-cause hospital mortality, ICU and hospital length of stay (LOS), the difference in P/F ratio between day one and day seven (not to be calculated for patients who are censored before seven days), 28 days ventilator-free days (VFD) (defined as days without mechanical ventilation till day 28 starting from day of enrollment, as long as the patient is alive); patients still mechanically ventilated at day 28, or died by day 28, will be assigned zero VFD. If the artificial airway is shifted from endotracheal tube to tracheostomy, they will still be considered mechanically ventilated until they are liberated from mechanical ventilation and are spontaneously breathing. With respect to a successful extubation rate, defined as extubated and not requiring re-intubation for 72 hours, tracheostomy is not considered successful extubation. Examples of adverse events will be hypersensitivity reactions - of any magnitude, abnormal lab investigations, specifically electrolytes and renal function tests, and volume of urine output.

Enrollment, randomization, and allocation concealment

After obtaining the informed consent of a legal guardian, randomization will be obtained via a phone call providing a study code, without breaking the concealment of allocation. Randomization will be performed using variable block sizes (4, 6, or 8), stratified by ARDS severity (mild, moderate, severe).

Blinding

Furosemide and saline are identical in appearance, color, and solution characteristics. The investigational medication will be prepared by an independent pharmacist in identical vials, labeled only with study code and patient identifiers, and delivered to the clinical area. The flow of patients' enrollment is depicted in Figure 1.

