Assuming a mortality rate of 40% in the control group [2,8], and aiming to detect an effect size of 10% absolute reduction in mortality in the intervention group with a power of 80% and type I error rate of 5%, we estimated the sample size to be 712 patients (356 in each group), with 10% inflation to compensate for possible loss of follow-up (patients transferred to other healthcare facilities), we plan to recruit a total of 784 patients, allocated in a 1: 1 ratio as 392 patients in each group.

Statistical plan

Intention-to-treat (ITT)-based analysis: Data of the patients will be analyzed in the group to which they were randomized, regardless of the actual intervention they received. Continuous variables will be summarized as mean ± standard deviation (SD) or median and interquartile range (IQR) depending on the normality assumption, tested for by the Shapiro-Wilk normality test. Discrete variables will be summarized as frequency (count) and percentage. Time-to-event data will be 28-day mortality as the event and duration since randomization as the time variable, with right censoring.

For the primary outcome, comparison between both groups for 28-day mortality will take place by the chi-square test of association, for secondary outcomes, groups will be compared by the chi-square test of association or Fisher’s exact test, according to data count in each cell of the two by two contingency table, while continuous variables will be compared between groups by the student's t-test or the non-parametric Wilcoxon Rank-Sum test.

We will perform a survival analysis using the time-to-event data, in the form of a Kaplan-Meier Survival curve as compared by the log-rank test.

As a sensitivity test for the primary outcome, we will fit two regression models. First will be a multinomial logistic regression model, using backward elimination to retain only variables with p-value < 0.1 and the severity of ARDS as the multinomial levels in the model. A multivariable proportional hazard model (Cox regression) will be carried out in a similar way, utilizing days from randomization to event as the time variable. Additionally, we will present a per-protocol analysis of the primary outcome.

A priori subgroup analyses will examine the primary outcome with regard to sex, the median age of the cohort, ARDS severity, and adjunct and rescue therapies used (such as corticosteroids, prone positioning, and ECMO).

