## Results

All results of group comparisons will be presented with either mean or percent difference, along with the corresponding 95% confidence interval (CI). The main results will be presented within the text of the results section while all results will be presented in table formats; the first dummy table outlines the baseline characteristics of the enrolled patients and the second dummy table will include the outcomes (dummy Tables 1, 2).

**Table 1 TAB1:** Dummy table showing baseline characteristics SOFA = Sequential Organ Failure Assessment, CFS = Clinical Frailty Scale, BMI = Body Mass index, CKD = Chronic Kidney Disease, CLD = Chronic Liver Disease, CPD = Chronic Pulmonary Disease, CHD = Chronic Heart Disease, PaO2 = Arterial Partial Pressure of Oxygen, FiO2 = Fraction of Inspired Oxygen, P/F = PaO2 / FiO2, PEEP = Positive End-Expiratory Pressure, CPAP = Continuous Positive Airway Pressure, ARDS = Acute Respiratory Distress Syndrome

Variable (mean±SD) or (n,%)	Furosemide Group (n=………)	Control Group (n=………..)
Age (years)		
Sex (Females)		
SOFA (Randomization)		
CFS		
BMI		
Comorbidities		
Diabetes		
Hypertension		
CKD		
CLD/Cirrhosis		
CPD		
Heart Failure / CHD		
Immunocompromised		
Malignancy		
Smoker		
ARDS Diagnosis and Precipitating Factors		
PaO2 (mm/Hg)		
FiO2 (decimal)		
P/F Ratio		
PEEP/CPAP (cmH2O)		
Bacterial Pneumonia		
Viral Pneumonia		
Sepsis / Septic Shock		
Trauma-Related		
Transfusion-Related		
Inhalational Injury		
Pancreatitis		
ARDS Severity		
Mild		
Moderate		
Severe		

**Table 2 TAB2:** Dummy table showing primary and secondary outcomes ICU = Intensive Care Unit, LOS = Length of Stay, P/F = Ratio of Arterial Partial Pressure of Oxygen to Fraction of Inspired Oxygen, VFD = Ventilator-Free Days, CI = Confidence Interval

Variable (mean±SD) or (n,%)	Furosemide Group (n=………)	Control Group (n=………..)	Mean/Percent difference (95% CI; p-value)
ICU Mortality Within 28 Days			
Hospital Mortality			
ICU LOS			
Hospital LOS			
P/F Ratio Change Within 7 Days			
28 Days VFD			
Successful Extubation			
Adverse Events			

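### The day-one-to-day-seven P/F change is tested without starting P/F or the P/F-based stratum, so the test is valid but conservative and its interval can be wider than needed

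*Protocol article*

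**What the plan says.** Study objectives (Protocol article, Materials and methods) lists among the secondary outcomes "the difference in P/F ratio between day one and day seven (not to be calculated for patients who are censored before seven days"). The Statistical plan then sets one rule for continuous secondary outcomes: "continuous variables will be compared between groups by the student's t-test or the non-parametric Wilcoxon Rank-Sum test". The two regression models in that section are sensitivity analyses of the primary outcome only. The endpoint has its own row in dummy Table 2, "P/F Ratio Change Within 7 Days", to be filled with a difference, a 95% CI and a p-value.

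Two other places matter. Under Results, "the first dummy table outlines the baseline characteristics of the enrolled patients", and P/F ratio is one of its rows. Under Enrollment, randomization, and allocation concealment: "Randomization will be performed using variable block sizes (4, 6, or 8), stratified by ARDS severity (mild, moderate, severe"). The severity levels are bands of the P/F ratio itself, as in "Mild: 200 mmHg < PaO2/FIO2 ≤ 300 mmHg" (Inclusion and Exclusion Criteria), with cut-points at 100 and 200 mmHg.

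**The concern.** Among the efficacy outcomes, this is the one built from a starting and a later value of the same measurement. The design treats P/F as important enough to stratify on. The analysis then uses neither the stratum nor the continuous starting value.

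A raw change score fixes the slope of day-seven P/F on starting P/F at 1. Entry is capped at 300 mmHg, so a slope below 1 is plausible. The change is then negatively related to the starting value. A two-sample test counts that predictable variation as noise, although stratified allocation has already kept most of it out of the difference between arms. The reported standard error is then larger than the real sampling variation.

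At stake is the width of one confidence interval and the power of one secondary test. The Introduction lists the P/F change among the favourable trends of the earlier COVID-19 trial, so readers will look at this row.

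**Working it through.** **The plan's own figure.** The article states no figure for the P/F endpoint. Its only sample size is for mortality, 40% against 30%, 80% power, two-sided 5%: n per group = [1.960·√(2·0.35·0.65) + 0.842·√(0.4·0.6 + 0.3·0.7)]² / 0.10² = 356, or 712 in total. Then 712 × 1.10 = 783.2, rounded up to 784. These match the plan, and the P/F point does not touch them.

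**Inputs.** From the article: the change score as endpoint, an unadjusted test, blocks of 4, 6 or 8 within three P/F bands, and two-sided alpha of 0.05. Assumed, because the article is silent: K = SD(day 7)/SD(day 1) from 1 to 1.5; correlation ρ from 0.3 to 0.7; 250 evaluable patients per arm; starting P/F drawn from a normal distribution with mean 160 and SD 60, truncated to 50–300 (SD about 54 after truncation).

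**Reported standard errors.** The t-test's error variance is proportional to 1 + K² − 2ρK, and that of ANCOVA to K²(1 − ρ²). The ratio of planned to ANCOVA standard error is √[(1 + K² − 2ρK) / (K²(1 − ρ²))]. For K = 1, ρ = 0.3 it is √(1.40/0.91) = 1.24. For K = 1.5, ρ = 0.7 it is √(1.15/1.1475) = 1.00. The power column is simulated under the planned stratified blocks and gives ANCOVA's power for an effect that the planned t-test detects with 80% power.

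| K | ρ | slope ρK | SE ratio, planned/ANCOVA | ANCOVA power |
|---|---|---|---|---|
| 1 | 0.3 | 0.30 | 1.24 | 91% |
| 1 | 0.5 | 0.50 | 1.15 | 88% |
| 1 | 0.7 | 0.70 | 1.08 | 85% |
| 1.25 | 0.3 | 0.38 | 1.13 | 87% |
| 1.25 | 0.5 | 0.63 | 1.06 | 83% |
| 1.25 | 0.7 | 0.88 | 1.01 | 80% |
| 1.5 | 0.3 | 0.45 | 1.07 | 84% |
| 1.5 | 0.5 | 0.75 | 1.02 | 81% |
| 1.5 | 0.7 | 1.05 | 1.00 | 80% |

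The planned standard error is thus 0% to 24% larger than ANCOVA's. Put the other way, ANCOVA's is 0% to 19% smaller (1 − 1/1.24 = 0.19).

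**Reported against true variation.** Stratification reduces the true sampling variation of the raw difference, and the t-test does not know this. Simulation with stratified blocks (4,000 runs, mmHg):

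| K | ρ | t-test: mean reported SE | t-test: true sampling SD | ANCOVA: mean SE | ANCOVA: true sampling SD | Type I error, t-test |
|---|---|---|---|---|---|---|
| 1 | 0.3 | 5.64 | 4.93 | 4.55 | 4.61 | 2.4% |
| 1 | 0.5 | 4.77 | 4.29 | 4.13 | 4.09 | 3.1% |
| 1 | 0.7 | 3.69 | 3.50 | 3.40 | 3.42 | 4.0% |
| 1.25 | 0.3 | 6.41 | 5.83 | 5.68 | 5.66 | 3.4% |
| 1.25 | 0.5 | 5.46 | 5.09 | 5.16 | 5.04 | 3.8% |

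In the other four scenarios the t-test's type I error is about 4.5% to 5%. ANCOVA stays near 5% throughout. Adding the stratum as a factor beside continuous P/F leaves its standard errors practically unchanged.

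At K = 1, ρ = 0.5, the reported standard error exceeds the true one by 4.77/4.29 = 1.11, or 11%. The true sampling SD falls only from 4.29 to 4.09 under ANCOVA, a variance reduction of 1 − (4.09/4.29)² = 9%. Most of the excess width is an overstated standard error.

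**Chance imbalance.** Without stratification the SD of the difference in mean starting P/F would be about 54·√(2/250) = 4.8 mmHg (5.4 with the untruncated SD of 60). With stratification it is about 2.3 mmHg. Each 1 mmHg of imbalance moves the change difference by (slope − 1). At slope 0.5, a one-SD imbalance moves it by 0.5 × 2.3 = 1.2 mmHg, against a reported standard error of 4.77.

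**The case against.** The best defence is that nothing here is invalid. In a randomised comparison, the difference in mean change is unbiased for the same quantity as ANCOVA, leaving aside who has a day-seven value. Its error is on the safe side. The sentence on tests is a general rule in a condensed article, and a fuller analysis plan might refine it. The gain depends on an SD ratio and a correlation that the article does not give. Entry P/F is capped and day-seven P/F is not, so an SD ratio above 1 is quite plausible, and there the gain shrinks towards nothing. The article itself says that secondary results are not to be taken as conclusive.

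Most of this stands and sets the weight of the point. It does not remove it. The article names the test, so a later plan would have to override it. The caution about secondary results is tied to the lack of multiplicity correction, and that is no reason to report an interval wider than the data require.

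A reader might infer three stronger things, and the documents support none of them:

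- That the planned test gives false positives or a biased estimate. Its type I error is at or below nominal.
- That baseline imbalance and regression to the mean will distort the result. Stratifying on P/F bands confines imbalance to within bands, and its effect is small.
- That 25% to 35% of the variance is truly lost (1 − 0.75/1.00 and 1 − 0.91/1.40 at K = 1). Those figures ignore the stratified allocation and hold only at an SD ratio of 1.

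**Conclusion.** The point holds as a minor one. The planned t-test of the P/F change is valid but conservative, because it ignores both the starting value and the variable on which allocation was stratified. Under the assumptions above, the planned standard error is about 0% to 24% larger than ANCOVA's, type I error is about 2% to 5%, and 80% power would become about 80% to 91%. The gain is close to nil when the slope of day-seven on starting P/F is near 1, and larger when it is well below 1.

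The size rests on assumed SDs, correlations and evaluable numbers, and on linear relations with normal errors. It describes the t-test. The rank-sum alternative ignores the same covariates but was not quantified. The primary mortality analysis and the sample size are unaffected.

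**What to change.** For this endpoint, replace the general rule with a linear model of day-seven P/F (or the change; the treatment effect is the same) on treatment arm, with pre-treatment P/F as a continuous covariate and ARDS-severity stratum as a factor. Report the adjusted mean difference with its 95% CI in the Table 2 row. If residuals are clearly non-normal, use log P/F or a rank-based model with the same covariates instead of the unadjusted rank-sum test. State that the covariate is the value before the first dose, since the article does not say whether the day-one reading is that value.

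The cost is one sentence in the Statistical plan and a few degrees of freedom, with no new data, visits or patients. It should be settled before unblinding. The change does not repair the exclusion of patients censored before day seven, which needs its own answer.

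### The first sensitivity model for mortality is misspecified as written, and the p < 0.1 elimination rule exempts neither treatment nor severity in either regression model

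*Protocol article*

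**What the plan says.** All of this is in the protocol article, Materials and methods.

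- **Endpoint** (Study objectives): "The primary objective is 28-day mortality in the ICU, starting from the day of randomization".
- **Primary test** (Statistical plan): "comparison between both groups for 28-day mortality will take place by the chi-square test of association".
- **Purpose of the models** (Statistical plan): "As a sensitivity test for the primary outcome, we will fit two regression models".
- **First model** (Statistical plan): a "multinomial logistic regression model, using backward elimination to retain only variables with p-value < 0.1 and the severity of ARDS as the multinomial levels".
- **Second model** (Statistical plan): "A multivariable proportional hazard model (Cox regression) will be carried out in a similar way", with days from randomisation to the event as the time variable.
- **Role of severity** (Enrollment, randomization, and allocation concealment): blocks of 4, 6 or 8, "stratified by ARDS severity (mild, moderate, severe").

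The plan does not name death as the dependent variable of the first model. It does not say that treatment or severity stays in regardless of its p-value.

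**The concern.** There are two separate faults.

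**Model type.** The levels of a multinomial logistic model are the categories of its dependent variable. Here the stated levels are mild, moderate and severe ARDS. These are fixed before randomisation and used to stratify it, so they cannot respond to treatment. The endpoint to be checked has two categories and needs a binary model.

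**Selection rule.** A rule that keeps only terms with p < 0.1, with no exemption stated, can remove the term the analysis exists to estimate. It can also remove the stratification factor. If treatment survives such a rule, its confidence interval and p-value ignore the selection step.

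The primary chi-square test is unadjusted. These two regressions are the only planned covariate-adjusted analyses of mortality, and that adjusted check is what is at stake.

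**Working it through.** **1. The dependent variable: two readings.**

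*Reading A, as worded.* "the severity of ARDS as the multinomial levels in the model" makes severity the outcome. With blocks of at most 8 within each stratum, only the last block can be incomplete, so the arms differ by at most 4 patients per stratum. The association between treatment and severity is therefore close to zero whatever treatment does to mortality.

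This was checked by simulating 2,000 trials for each of three true effects (0, 5 and 10 percentage points). Each trial had 712 patients, randomised in permuted blocks of 4, 6 or 8 within severity. The test was a 2-df likelihood-ratio test of treatment, as the only predictor, against severity. Treatment had p ≥ 0.1 in 2,000 of 2,000 trials at every effect size, and the smallest p was about 0.95. The severity mix of 30/45/25% is an assumption. Control mortality of 35/40/45% by severity follows the figures in the article's Discussion. The result comes from the stratified blocks, not from these inputs.

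*Reading B, as probably intended.* Death is the outcome and severity is a three-level predictor or stratum. The model is then binary logistic and the word multinomial is wrong. The elimination rule remains.

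**2. The plan's own sample size.** Inputs from the Sample size calculation section: 40% versus 30%, 80% power, 5% type I error (two-sided, per the Statistical plan).

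n per arm = [1.9600·√(2·0.35·0.65) + 0.8416·√(0.40·0.60 + 0.30·0.70)]² / 0.10² = [1.3221 + 0.5646]² / 0.01 ≈ 355.9, so 356. This matches the stated 356 per group.

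**3. How often "using backward elimination to retain only variables with p-value < 0.1" would drop treatment, under Reading B, if it applies to treatment.** With 356 per arm, control mortality 0.40, treated-arm mortality p_T and difference δ = 0.40 − p_T:

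- p̄ = (0.40 + p_T)/2
- SE0 = √(2·p̄(1 − p̄)/356)
- SE1 = √([0.24 + p_T(1 − p_T)]/356)
- P(dropped) = Φ((1.645·SE0 − δ)/SE1) − Φ((−1.645·SE0 − δ)/SE1)

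At p_T = 0.30: SE0 = 0.03575 and SE1 = 0.03555. (0.0588 − 0.10)/0.03555 = −1.159, and Φ(−1.159) = 0.123. The second term is negligible.

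At p_T = 0.35: SE0 = 0.03629 and SE1 = 0.03624. (0.0597 − 0.05)/0.03624 = 0.268, and the probability is 0.604.

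| Treated-arm mortality | P(dropped), normal approximation | Simulated, logistic model of death adjusted for severity |
|---|---|---|
| 40% (no effect) | 0.90 | 0.91 |
| 37.5% | 0.82 | not run |
| 35% | 0.60 | 0.61 |
| 32.5% | 0.33 | not run |
| 30% (design effect) | 0.12 | 0.12 |

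Cross-check from the design alone: 80% power implies a drift of 1.960 + 0.842 = 2.802, and Φ(1.645 − 2.802) = Φ(−1.157) = 0.124.

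**4. Sensitivity to sample size.** With all 392 per arm evaluable, the drift is 2.802·√(392/356) = 2.94. Φ(1.645 − 2.94) = 0.098, so about 10% instead of 12%.

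**The case against.** **The text says the model is for the primary outcome.** That points to death as the intended outcome. The Cox model is to be fitted by the same approach with time to event as its outcome, which also suggests severity as a predictor or stratum. This stands. A reader might infer that the plan definitely models severity and ignores death, but the document does not establish that. What remains is that the wording is wrong on both readings.

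**Removing treatment is an inference.** Such models usually exist to adjust the treatment comparison, and a fuller plan may force treatment in. This stands in part. A reader might infer that treatment will be removed, but the article does not say so. It does state a rule confined to terms below 0.1 with no exemption, so the stated rule permits removal.

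**Little is lost.** The chi-square, log-rank and per-protocol analyses do not use these models, and the Results section promises a difference with a 95% confidence interval for every group comparison. This stands. A reader might infer that the primary conclusion is unsafe, and that would be wrong. The 90% under no effect also means only that the treatment p-value is at least 0.1, so no positive result disappears. What would be missing is the adjusted estimate with its interval, which readers need most when the effect is small or absent.

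**Selection distortion has no size attached.** This is correct. If treatment is kept and only baseline covariates are selected, randomisation limits the bias in the treatment estimate.

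**Conclusion.** The concern holds as a should-fix. The first sensitivity model is misspecified as written. Either it makes a baseline stratification factor the dependent variable and carries no information on mortality, or it misnames a binary logistic model of death. This is a stated specification, not a detail left to a later document.

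The elimination rule leaves treatment and severity unprotected in both regressions. If it is applied to treatment, treatment is lost in about 12% of trials at 40% versus 30%, about 60% at 40% versus 35%, and about 90% under no effect. These figures assume 356 evaluable patients per arm, a two-sided p-value for treatment and little change in its precision from other covariates. The damage is confined to the adjusted supportive analyses.

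**What to change.** Replace the first model with a binary logistic regression of the primary endpoint as the protocol defines it, ICU mortality within 28 days of randomisation. It should not become death by day 28 in any location, which would change the endpoint being checked. Force in treatment and three-level ARDS severity. Add a short prespecified list of baseline covariates already in dummy Table 1, for example age and SOFA. Leave out the P/F ratio, since its cut-points define severity. Use no stepwise selection.

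Fit the Cox model with treatment forced in, the same fixed covariates, and severity as a covariate or as a stratum.

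Treatment is then estimated in every trial. The cost is two sentences in the statistical plan, written before the data are analysed, with no additional data or patients.

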There will be no correction for multiple testing; accordingly, results of secondary outcomes and sub-group analyses should not be considered conclusive and must be cautiously interpreted.

All statistical tests are two-sided and considered statistically significant if the p-value is <0.05.

Interim analysis and stopping rules

We will perform one interim analysis when 50% of the sample size is recruited, to assess the efficacy of the intervention, with the possible early stopping of the trial based on O’Brien-Fleming alpha spending functions [29]. The stopping rules are: 1- Stopping for superiority: If the interim analysis results in a critical z-score of +2.963 or more, yielding a p-value of 0.0031 or less; 2- Stopping for harm: If the interim analysis results in a critical z-score of -2.963 or less, yielding a p-value of 0.0031 or less; 3- Stopping for futility: If the interim analysis results in a critical z-score between +0.595 and -0.595, corresponding to a p-value of 0.55 (Figure 2).

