**Figure 2 FIG2:**
[figure not shown]
Trial stopping bounds The trial may be stopped at the first interim analysis for harm or benefit (p = 0.0031) or futility (p = 0.55).

Ethical considerations

This protocol was approved by the institutional review board of King Saud Medical City (Riyadh, Saudi Arabia) (reference number: H1RI-19-Aug24-01). The duration of the initial IRB approval was three months and this is extendable after we present a progress report indicating that the trial is still ongoing. The protocol was registered with the ISRCTN registry (registration number ISRCTN16516753; dated March 23, 2025). The study will abide by the general rules of research subject protection outlined by the Declaration of Helsinki.

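### Minor: the blanket p < 0.05 rule conflicts with the O'Brien-Fleming design, whose final bound is p < 0.0490; with non-binding futility, two-sided type I error is 5.10%, not 5%

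*Protocol article*

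**What the plan says.** The Sample size calculation in the protocol article plans the trial "with a power of 80% and type I error rate of 5" (per cent). The last sentence of the Statistical plan applies one threshold to everything: "All statistical tests are two-sided and considered statistically significant if the p-value is <0.05". It makes no exception for the primary outcome, 28-day mortality compared by a chi-square test.

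The next section, Interim analysis and stopping rules, plans one efficacy look at half of recruitment under O'Brien-Fleming alpha spending. The superiority rule reads: "If the interim analysis results in a critical z-score of +2.963 or more, yielding a p-value of 0.0031 or less". The harm rule mirrors it at -2.963, and futility is the zone between -0.595 and +0.595. The Figure 2 caption says: "The trial may be stopped at the first interim analysis for harm or benefit (p = 0.0031) or futility (p = 0.55".

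The text gives no separate threshold for the final primary test. The Results section promises 95% confidence intervals for all group comparisons.

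**The concern.** An alpha-spending design for two looks consists of two linked bounds. Part of the 5% is spent at the interim, and the final bound must be slightly stricter than 1.960 so that the two together spend 5%. The protocol prints the first bound, and its general rule then gives the final test the full 0.05.

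This concerns the decision rule for the trial's only confirmatory claim. A final p-value between 0.0490 and 0.0500 would be a significant mortality difference under the Statistical plan and a non-significant one under the spending function named in the following section. An ordinary 95% interval would side with the looser rule. The conflict should be settled before anyone sees unblinded data.

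**Working it through.** **Inputs from the protocol article.** Two-sided alpha 0.05; power 80%; mortality 40% against 30%; 356 per arm (712), inflated to 784; one look at information fraction t = 0.5; interim efficacy and harm bounds ±2.963; futility zone |z| < 0.595; final threshold p < 0.05, that is |z| > 1.960.

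**1. Sample size reproduced.** With pooled variance under the null, n per arm = [1.960·√(2·0.35·0.65) + 0.8416·√(0.40·0.60 + 0.30·0.70)]² / 0.10² = (1.3221 + 0.5646)² / 0.01 = 355.9, so 356 per arm and 712 in total. Then 356 × 1.10 = 391.6, so 392 per arm and 784. The figures come from a single-look calculation at 1.960.

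**2. Interim bound reproduced.** Lan-DeMets O'Brien-Fleming spending with 0.025 per side: the spend per side at t = 0.5 is 2·[1 − Φ(2.2414/√0.5)] = 0.001525. This gives z = 2.9626 and a two-sided spend of 0.00305, matching the printed 2.963 and 0.0031. The design is therefore identified.

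**3. Overall type I error with a final test at 0.05.** Under the null, Z1 and Z2 are bivariate normal with correlation √0.5. With futility non-binding:

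- P(|Z1| ≥ 2.963) = 0.00305
- P(|Z1| < 2.963 and |Z2| > 1.960) = 0.04794, by numerical integration
- Total = 0.05099, or 5.10%

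A simulation of 20 million pairs of normal test statistics gave 0.0510.

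**4. Final bound that restores 5%.** Solving P(|Z1| ≥ 2.963 or |Z2| ≥ c) = 0.05 gives c = 1.9686, a two-sided p of 0.0490.

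**5. Effect of the futility rule.** If every trial with |Z1| < 0.595 stopped without rejection, the total would be 0.00305 + 0.04415 = 0.0472. To see which version produced the printed futility bound, assume O'Brien-Fleming beta spending with total beta 0.20 (the protocol does not name a beta-spending function) and solve both versions at 80% power:

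| Version | Futility bound | Final bound | Final p |
|---|---|---|---|
| Non-binding | 0.595 | 1.969 | 0.0490 |
| Binding | 0.576 | 1.935 | 0.0530 |
| Protocol text | 0.595 | 1.960 (general rule) | 0.05 |

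Only the non-binding version yields the printed ±0.595. The general rule's 1.960 belongs to neither version.

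**6. Timing.** With ±2.963 held fixed, the total is 5.14% at t = 0.4 and 5.06% at t = 0.6. If the interim bound is recomputed from the spending function and the final test stays at 0.05, it is 5.03% at t = 0.4 and 5.23% at t = 0.6.

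**7. Power cost.** With 40% against 30% and futility ignored, moving the final bound from 1.960 to 1.969 takes power from 80.4% to 80.2% at 356 per arm, and from 84.0% to 83.8% at 392 per arm.

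**The case against.** **Futility recovers the alpha.** The futility rule is listed beside the superiority and harm rules, and if it is obeyed the error is 4.7%. Partial use would be enough: futility removes 0.0510 − 0.0472 = 0.0038, the excess is 0.00099, and 0.00099/0.0038 is about 26%. Acting on futility in roughly a quarter of the cases that meet it would bring the total back to 5%. The permissive wording also covers efficacy and harm, so on its own it is weak evidence that futility is optional. This stands as a condition on the 5.10%. It does not remove the point, because a discretionary stop cannot be counted on to control error, and the printed ±0.595 comes from the non-binding calculation, whose own final bound is 1.969.

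**Figure 2 may show the final bound.** The figure is not reproduced in the text available, so a reader who infers that the plan has no final bound at all goes too far. The statement holds for the text only. If the figure does plot 1.969, the general 0.05 sentence contradicts it and still needs correcting.

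**The article is condensed.** The spending function, alpha and timing together determine the final bound, and printing it could be left to an analysis plan. That is fair for an omission. Here, however, the article states a threshold, and that threshold disagrees with the design.

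**No correction for multiple testing is announced.** The protocol draws the consequence only for secondary outcomes and subgroups. Adopting alpha spending shows the intent to control error across looks at the primary outcome.

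**Stronger readings.** A reader might add 0.0031 and 0.05 to get 5.31%; that ignores the correlation between looks. A reader might also simulate the chi-square test itself at a 40% death rate, find about 5.2%, and attribute all of the excess to the final threshold. Most of it is discreteness: the exact size at 356 per arm with no interim look is already 5.10%, and the corrected bound still leaves about 5.15%. Such simulations are not evidence for this point.

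**Conclusion.** Wrong as written, and minor. The general p < 0.05 rule conflicts with the alpha-spending design the protocol adopts. The nominal overall two-sided type I error is 5.10% against the stated 5%. This rests on three assumptions: the interim falls at half the information, futility is non-binding, and the test statistics are approximately normal. With futility binding and always obeyed it would be 4.7%, and there would be no inflation.

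The excess is about 0.1 percentage point, so under the null about one trial in a thousand would be decided differently. The documents do not support reading this as a serious loss of error control. What needs settling is the ambiguity in the primary decision rule.

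**What to change.** In the Statistical plan, exempt the primary outcome from the general 0.05 rule. In Interim analysis and stopping rules, state that:

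- at the final analysis the primary outcome is significant if |z| ≥ 1.969 (two-sided p < 0.0490);
- if the interim is not at 50% information, both bounds are recomputed from the O'Brien-Fleming spending function;
- the futility bound is non-binding.

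Report the primary risk difference with a 95.1% confidence interval (1 − 0.0490 = 0.951) so that interval and test agree. Keep p < 0.05 for all other tests. If Figure 2 shows a final bound, check that it agrees.

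The cost is a few lines of text and about 0.2 points of power, with no extra patients. The new bound corrects the spending only; it does not remove the discreteness of the chi-square test.
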